### Alternative statistical models and sensitivity analyses

First, if the generalized mixed effects model does not converge or is deemed not sufficient, an analogous generalized estimating equation (GEE) model will be used in which the correlation is adjusted for using the R matrix (within-subject correlation), either unstructured or autoregressive (AR (1)). Second, a recurrent time to event model with ordinal outcome (the continuation ratio approach) [14] will be fit. This approach models the risk for the *j*th event (e.g., a certain category of pressure injury at a specific f/up measurement) ignoring any previous events, but accounting for subject as random effect, and can be modeled using an event- stratified proportional hazards regression model.

#### Treatment effect heterogeneity

We will assess treatment effect (IES device versus control) heterogeneity for the primary outcome across levels of various baseline factors (Additional file 4) using tests for interaction (treatment-by-baseline interaction). Primary result will be the interaction *P*-value and corresponding estimate of the interaction effect. We will also test and report the treatment effect and confidence interval within levels of each factor.

### Secondary endpoint analyses

We will assess the treatment effect of IES vs standard care on time to event outcomes (time to resolution of ulcer, time to worsening of ulcer, time to discharge alive, and mortality) using Cox proportional hazards regression and reporting results as hazard ratio and 95% confidence interval, with the proportional hazards assumption tested using the treatment-by-log(time) interaction as well as graphical displays of the hazard of the outcome over time for the overlayed treatment groups. Kaplan–Meier analyses with 95% confidence bands and the log-rank test will also be used.

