**Methods:**

The Pressure Injury Treatment by Intermittent Electrical Stimulation (PROTECT-2) trial will be a parallel-arm multicenter randomized trial to test the hypothesis that IES combined with routine care reduces sacral and ischial pressure injury over time compared to routine care alone. We plan to enroll 548 patients across various centers. Hospitalized patients with stage 1 or stage 2 sacral or ischial pressure injuries will be randomized to IES and routine care or routine care alone. Wound stage will be followed until death, discharge, or the development of an exclusion criteria for up to 3 months. The primary endpoint will be pressure injury score measured over time.

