#### Secondary

Secondary outcomes are time to event endpoints (time to resolution of ulcer, time to worsening of ulcer, time to discharge alive, daily subjective evaluation of ulcer, and mortality).

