#### Primary outcome

The primary outcome will be sacral and ischial pressure injury assessed with the SPI instrument score (range 0–4) over time. For the statistical analysis of clinical course, unstageable injuries will be assigned a score of 3 (equivalent to stage III injuries). For ulcers that progress to deep tissue injuries (DTI), these will be assigned a score of the previous ulcer stage plus one. If a patient experiences multiple sacral/ischial pressure injury simultaneously, the most severe injury will be used for analysis. The primary outcome will be based on the combined stage 1 and stage 2 ulcer types.

Patients will be assessed twice daily by the bedside nurse for pressure injury location and stage from study entry to discharge from the hospital or at least 30 days, whichever comes first. This is a standard wound care evaluation protocol for nursing. Wound care nursing specialist consultation staging will be used instead of bedside nursing staging should a discrepancy occur. If SPI scores are available after discharge and within the 30 days, those data will be included in the analyses as well, even if the SPI are healed or at the worst stage.

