#### Primary outcome analyses

We will assess the efficacy of an IES system added to the standard care versus standard wound care on sacral and ischial pressure injury scores measured over time using a generalized mixed effects ordinal regression cumulative logit model which considers treatment and time (categorical) as fixed effects and subject as a random effect and accounts for (1) the ordinal nature of the data and (2) the within-subject correlation over time. The model will allow differing number of measurements and lengths of follow-up for patients but will assume that shorter follow-up or dropout is largely at random and not due to either improvement or worsening of SPI symptoms. We will also assess the treatment-by-time interaction to assess whether the treatment effect is consistent over time. Given a significant interaction, we will assess the treatment effect at various time points, although the primary analysis will be the treatment effect collapsed over time.

Results will be reported as a proportional odds ratio which estimates the odds of an IES-treated patient having a higher (worse) score than a randomly chosen standard care patient. For example, an odds ratio of 0.6 would mean the treatment was associated with an estimated 40% lower odds of an EIS-treated patient having a higher score compared to standard care; correspondingly, a treated patient has a 40% higher odds of having a lower (better) score compared to a standard care patient.

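### Kaplan-Meier for resolution, worsening and discharge alive ignores competing death and discharge; cumulative incidence curves should replace it, and the mortality window should be stated

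*Protocol article*

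**What the plan says.** The protocol article's Secondary outcomes section lists the endpoints: "Secondary outcomes are time to event endpoints (time to resolution of ulcer, time to worsening of ulcer, time to discharge alive", followed by a daily subjective ulcer evaluation and mortality. Under Secondary endpoint analyses, resolution, worsening, discharge alive and mortality all receive one method: "time to discharge alive, and mortality) using Cox proportional hazards regression and reporting results as hazard ratio and 95% confidence interval". The section ends: "Kaplan–Meier analyses with 95% confidence bands and the log-rank test will also be used". Neither this section nor the one on alternative models and sensitivity analyses names a cumulative incidence estimator or any other competing-risk method.

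Follow-up is described in two places. The abstract's Methods paragraph says: "Wound stage will be followed until death, discharge, or the development of an exclusion criteria for up to 3 months". The Primary outcome section has twice-daily nursing assessment "from study entry to discharge from the hospital or at least 30 days, whichever comes first", and adds: "If SPI scores are available after discharge and within the 30 days, those data will be included in the analyses as well". Scores after discharge are therefore used when they happen to exist.

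The article does not state the censoring rule for the secondary endpoints, or whether vital status is followed after discharge.

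**The concern.** A patient who dies can no longer be discharged alive, heal or worsen. A patient who goes home usually stops contributing wound stages. Kaplan-Meier with those patients censored treats them as if they would later have the event at the same rate as patients still in hospital. One minus Kaplan-Meier then describes a setting in which nobody dies or leaves, not the share of enrolled patients who had the event.

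Resolution and worsening are the results that clinicians will read most directly in a healing trial. If the curves are read as the percentage healed by day 30, that percentage is too high. If IES changes the timing of discharge, the contrast between arms can also differ from the contrast in patients who actually healed or worsened.

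**Working it through.** **Inputs.** The article gives no event rate, death rate or length of stay for these endpoints, so there is no stated figure to reproduce. Every hazard below is an assumption (constant, per day). The horizons come from the article: 30 days (Primary outcome) and 3 months, taken as 90 days (abstract).

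**Formulas.** With event hazard a, competing hazard c and horizon T:
- one minus Kaplan-Meier, competing event censored: 1 − exp(−aT)
- cumulative incidence: a/(a+c) × [1 − exp(−(a+c)T)]

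**Resolution, a = 0.05, day 30.** Kaplan-Meier: 1 − exp(−1.5) = 77.7%. Cumulative incidence at c = 0.02: 0.05/0.07 × [1 − exp(−2.1)] = 62.7%. The other rows follow in the same way.

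| Endpoint | a | c | Day 30: KM | Day 30: cum. inc. | Day 90: KM | Day 90: cum. inc. |
|---|---|---|---|---|---|---|
| Resolution | 0.05 | 0.02 | 77.7% | 62.7% | 98.9% | 71.3% |
| Resolution | 0.05 | 0.05 | 77.7% | 47.5% | 98.9% | 50.0% |
| Resolution | 0.05 | 0.10 | 77.7% | 33.0% | 98.9% | 33.3% |
| Worsening | 0.005 | 0.02 | 13.9% | 10.6% | 36.2% | 17.9% |
| Worsening | 0.005 | 0.05 | 13.9% | 7.3% | 36.2% | 9.0% |
| Worsening | 0.005 | 0.10 | 13.9% | 4.6% | 36.2% | 4.8% |
| Discharge alive (death competing) | 0.05 | 0.001 | 77.7% | 76.8% | 98.9% | 97.0% |
| Discharge alive (death competing) | 0.05 | 0.01 | 77.7% | 69.6% | 98.9% | 83.0% |

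The direction is the same in every row. With slow exit the gap is small: resolution at a = 0.05 and c = 0.005 gives 77.7% against 73.5% at day 30.

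**Which exit rates are plausible.** Table 2 plans for 10, 20 or 40 measurements per patient, and assessment is twice daily. If every assessment counts, that is about 5, 10 or 20 days of observation, or exit hazards near 0.20, 0.10 and 0.05. This is only a rough guide, because the table is a planning grid and not a forecast of stay. It does suggest that very slow exit is the less likely case. At c = 0.20, resolution by day 30 is 0.05/0.25 × [1 − exp(−7.5)] = 20.0%.

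**Mortality, only if deaths are counted in hospital and discharge is censored.** Death hazard 0.01 and discharge hazard 0.08: Kaplan-Meier gives 1 − exp(−0.3) = 25.9%; cumulative incidence is 0.01/0.09 × [1 − exp(−2.7)] = 10.4%.

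**What the Cox ratio does and does not show.** Let the worsening hazard be 0.005 in both arms, so the cause-specific hazard ratio is 1, and let the exit hazard be 0.04 in one arm and 0.06 in the other. By day 30 the cumulative incidence is 0.005/0.045 × [1 − exp(−1.35)] = 8.2% in the first arm and 0.005/0.065 × [1 − exp(−1.95)] = 6.6% in the second. Kaplan-Meier shows 13.9% in both. The ratio is correct for the hazard, but it does not show the difference in patients who worsened under observation.

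**The case against.** The strongest reply is that the censoring rule is inferred. Nothing in the article says that death or discharge will be treated as uninformative censoring for these endpoints. The one assumption of that kind, that the model "will assume that shorter follow-up or dropout is largely at random and not due to either improvement or worsening of SPI symptoms", belongs to the primary mixed model. An analysis plan that is not shown could keep deaths in the risk set for discharge alive, which removes the bias within the named methods. This stands in part: the rule is unstated, and discharge alive may already be handled well. It does not dispose of the point for resolution and worsening, because the article fixes the estimator and ordinary Kaplan-Meier censors at the competing event.

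Second, an ulcer can heal or worsen at home, and some scores after discharge will be used. If the target is resolution by a fixed day wherever the patient is, discharge is censoring rather than a competing event, and what matters is whether it is independent of healing. That is a fair point about the target. But scores after discharge enter only when available, death competes under either target, and the article does not say which target is meant.

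Third, a reader might infer that the Cox and log-rank results are invalid. They are not. With competing events censored, the Cox ratio is a valid cause-specific hazard ratio and the log-rank test compares cause-specific hazards. Neither overstates a probability.

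Fourth, a reader might infer that mortality is certainly overstated. The article says only mortality, and the abstract's limit on follow-up concerns wound stage. If vital status is known to a fixed day for everyone, death from any cause has no competing event and the planned methods are correct.

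**Conclusion.** The point holds for the Kaplan-Meier probabilities of resolution, worsening and discharge alive when competing events are censored, and for mortality only if deaths are counted in hospital. The direction is certain wherever competing events occur and are censored. The size is not: the documents give no rates, so a general claim that the probabilities are greatly overstated is unsupported. Under the assumed hazards in the table, the day-30 excess for resolution is 15 to 45 points at exit hazards of 0.02 to 0.10, for worsening about 3 to 9 points, and for discharge alive about 1 to 8 points. The Cox ratios need a correct label and a companion ratio, not replacement. These are secondary endpoints; the primary analysis and the planned 548 patients are untouched.

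**What to change.** - **Resolution and worsening:** replace the Kaplan-Meier curves with Aalen-Johansen cumulative incidence curves by arm, with confidence bands, counting death and discharge without the event as competing events. State that the target is the event during observed follow-up, and how scores after discharge enter.
- **Discharge alive:** use a cumulative incidence curve with death competing, or keep deaths in the risk set to the end of the window. Say which.
- **Cox models:** label the hazard ratios cause-specific and report the ratio for the competing event alongside. Fine-Gray models and Gray's test are optional complements, on which statisticians differ.
- **Mortality:** state the window. If in-hospital, treat discharge alive as competing. If vital status is known to a fixed day for all patients, Kaplan-Meier and Cox may stay.
- **Horizon:** reconcile the 30 days and the 3 months, since the curves need one stated end.

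The cost is some wording and a few extra lines of analysis. No new data are needed, unless fixed-day mortality is chosen and vital status after discharge is not already collected, which the article does not show.

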#### Exploratory endpoints

We will assess cost effectiveness of IES vs standard care within a subset of the patients studied. We will measure incremental cost-effectiveness ratios (ICERS) between traditional care and IES interventions in the treatment of pressure ulcers. Safety assessment is as follows: results from each of the 5 possible side effects listed on Patient and Assessor Questionnaire will be summarized as (1) proportion of patients ever having the event across their follow-ups, (2) severity grade across follow-ups for those having the event, and (3) severity grade for all patients, assigning a 0 to those without the event. Severity grade will be summarized using median [quartiles] and mean (SD). Confidence intervals within and between randomized groups will be estimated using bootstrap resampling with replacement to account for within-subject correlation across measurements.

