#### Significance level

The significance level will be 0.05 for all hypothesis testing and will be controlled at 5% across any multiple comparisons using appropriate multiple testing procedures. Two-sided tests for superiority will be used throughout.

For the statistical analysis of clinical course, unstageable injuries will be assigned a score of 3 (equivalent to stage III injuries). If a patient experiences multiple sacral/ischial pressure injury simultaneously, the most severe injury will be used for analysis.

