### Interim analysis

Interim analyses will be performed at each 25% of the planned enrollment using a group sequential design assessing the treatment effect on the primary outcome for efficacy and futility. We will use a gamma spending function with gamma parameters − 4 for efficacy and − 1 for futility. Stopping boundaries will be statistically non-binding; statistical accommodation for this option was made in the sample size calculations. The decision whether to stop a study at any interim analysis would be made by the DSMB, which would consider not only the statistical boundaries but other information as well. For example, if a futility or efficacy boundary was crossed at the first look, the DSMB might consider continuing the trial to obtain a more precise estimate of the treatment effect.

All data and results will be submitted to the data and safety monitoring board (DSMB) for review on an A versus B basis unless the DSMB requests to be unblinded. The DSMB is made up of physicians from multiple trial sites and a statistician (Additional file 5). The committee will assess any possible safety concerns, efficacy, and futility and advise if discontinuation is warranted and will meet at least yearly. DSMB members are independent from the sponsor and report to and communicate with the IRB and the steering committee.

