**C. Patients starting at stage II** ***N***** = 616 fixed (697 with interims)**					
	**0**	**I**	**II**	**III**	**IV**
**Intervention**	**80**	**0**	**17.5**	**2.5**	**0**
**Control**	**70**	**0**	**20**	**5**	**5**

Hypothetical percent in each pressure ulcer score category by treatment arm, for smallest clinically important effects: overall (A), for stage I (B), and stage II (C)

Table 2 gives total sample size for the combined stages in Table 1 (A), varying the number of measurements per subject (10, 20, 40) and varying ICC (0.2, 0.5, 0.8). The ICC is expected to be relatively high, so the recommended minimum sample size is 548 total (274/gp) for the overall treatment effect combining stages 1 and 2. However, since sufficient power is desired for each of the 2 starting strata, stage I and stage II, roughly the same sample size (548) should be achieved for each strata (see Table 2 for stage I and stage II strata). Therefore, a total maximum (accounting for interim analyses) sample size of approximately 1100 patients was recommended for this trial.

**Table 2 Tab2:** Sample size for varying # measurements and ICC. Data = *N* total. Starting with *N* = 668 total observations (Table 1 (A)), what is the required *N* subjects accounting for ICC and expected number of measurements/subject?

Patient sample	*N* measurements per patient	ICC		
		**.2**	**.5**	**.8**
**Combined stages **Table 1** (A) effect**	**10**	*188*	*368*	*548*
	**20**	*162*	*351*	*542*
	**40**	*148*	*344*	*538*
**Stage I start **Table 1** (B) effect**	**10**	174	342	510
	**20**	150	326	504
	**40**	138	318	500
**Stage II start **Table 1** (C) effect**	**10**	196	384	572
	**20**	168	366	564
	**40**	154	358	562

*N* = 668 assumed 1 measurement per patient (Table 1)

*ICC* intraclass correlation

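### As written, the bootstrap interval also covers the per-patient side-effect proportions, where it has zero width if an arm has no events and covers poorly if events are very rare

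*Protocol article*

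**What the plan says.** The safety assessment is described in the protocol article under Exploratory endpoints. It states that "results from each of the 5 possible side effects listed on Patient and Assessor Questionnaire will be summarized as" three quantities. The first is the "proportion of patients ever having the event across their follow-ups". The second is the severity grade among patients who had the event. The third is the severity grade in all patients, with 0 for those without the event. After saying how severity will be described, the paragraph ends: "Confidence intervals within and between randomized groups will be estimated using bootstrap resampling with replacement to account for within-subject correlation across measurements".

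That sentence is not limited to the severity summaries. The article names no other interval for the proportions, makes no provision for zero or sparse counts, and does not say which bootstrap interval (percentile, basic, normal or BCa) is meant.

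**The concern.** The stated reason for the bootstrap is correlation between repeated measurements on the same patient. Once a patient is reduced to ever or never having had the event, there is one observation per patient and no such correlation is left. For this summary the bootstrap gains nothing, and it behaves badly at low counts because resampling cannot produce events that the sample does not contain.

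An empty arm would be reported as 0% with a zero-width interval, which states certainty where the data only bound the rate. In a between-arm comparison, an empty arm would add no uncertainty at all. The Adverse event reporting section limits adverse events otherwise to skin irritation and allergies. For non-skin items, such as the feeling of electric shock, these questionnaire summaries are therefore the main quantitative statement on side effects.

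**Working it through.** **Inputs.** The arm size comes from Sample size considerations: "so the recommended minimum sample size is 548 total (274/gp"). The same section also says that a maximum "sample size of approximately 1100 patients was recommended for this trial", or about 550 per arm. The confidence level is taken as 95%, from "The significance level will be 0.05 for all hypothesis testing" under Significance level. The article gives no side-effect rates, so the true rates below are assumptions.

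**Reproducing the denominator.** With 10 measurements per patient and ICC 0.8, the article's design effect gives 668 × (1 + 9 × 0.8)/10 = 547.8, rounded up to 548, or 274 per arm. This agrees with Table 2.

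**Zero events.** Resampling n patients of whom x had the event gives a bootstrap count that is Binomial(n, x/n). At x = 0 this is always 0. Percentile, basic, normal and BCa intervals are then all 0% to 0%, at any n and any number of resamples. The comparators at 0 events are:

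- Exact (Clopper-Pearson) upper limit, 1 − 0.025^(1/n): 1.34% at n = 274 and 0.67% at n = 550.
- Wilson upper limit, z²/(n + z²) = 3.84/(274 + 3.84) = 1.38% at n = 274.
- Both arms empty: the bootstrap difference interval is 0 to 0; Newcombe's is −1.38 to +1.38 percentage points.

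**Coverage within an arm.** For each x from 0 to n, take the 2.5% and 97.5% quantiles of Binomial(n, x/n)/n. Then add up the Binomial(n, p) probabilities of those x whose interval contains p. For n = 274 and a percentile bootstrap:

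| Assumed true rate | P(0 events) | Percentile bootstrap coverage |
|---|---|---|
| 0.1% | 76.0% | 24.0% |
| 0.2% | 57.8% | 42.0% |
| 0.5% | 25.3% | 74.4% |
| 1% | 6.4% | 92.9% |
| 2% | 0.4% | 90.3% |
| 3% | 0.0% | 90.6% |
| 5% | 0.0% | 94.6% |
| 10% | 0.0% | 95.3% |

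Clopper-Pearson coverage is at least 95.7% at every rate tried, from 0.1% to 20%. At the lowest rates nearly all of the bootstrap shortfall is the chance of an empty arm: at 0.5%, 0.995^274 = 25.3%, which alone caps coverage at 74.7%. The other bootstrap types do no better there (73% to 75% at 0.5%). At 1% the basic interval does worse than the percentile interval (75.8%).

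**Coverage between arms** (percentile, 274 per arm, 4,000 simulated trials):

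- 0.5% against 0%: 74.9%
- 1% against 0%: 93.1%
- 0.5% against 0.5%: 97.8%
- 1% against 1%: 95.5%
- 2% against 1%: 94.6%

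Marked under-coverage appears only with one arm at zero and the other very low.

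**The case against.** **The sentence may be meant for severity only.** It follows directly on the description of severity grades, and its rationale fits repeated grades best. On that reading the article gives no interval method for the proportions, which a condensed article may leave to the full protocol or analysis plan. This is a fair reading of intent and lowers the weight of the point. It does not remove it, because the text as it stands covers all three summaries and a reader following it would bootstrap the proportions.

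**Rarity is not shown.** The items include sleep disturbance, discomfort and redness, and a patient counts if the item is ever reported on a daily questionnaire. Cumulative rates in the device arm may well be several per cent, where the bootstrap is adequate. This stands. A reader might infer that the side-effect intervals in general fall far below 95% coverage; the figures do not support that beyond about 0.5% per arm at full size.

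**The natural example is mild.** Electric-shock sensation in an unstimulated arm is close to a structural zero, so ignoring that arm's uncertainty does little harm. This too stands, and it leaves as the cases that matter an empty or nearly empty device arm and genuinely uncommon reactions.

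**Monitoring decisions.** A reader might infer that faulty intervals would mislead the monitoring board, since under Interim analysis "All data and results will be submitted to the data and safety monitoring board (DSMB) for review on an A versus B basis". The documents do not support that step. The stopping boundaries concern the primary outcome, and nothing ties a safety decision to these intervals. Skin irritation and allergies are also captured separately as graded adverse events.

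**Conclusion.** The point holds in a limited form. The zero-event result is certain and does not depend on the bootstrap type: 0% to 0%, against an exact upper limit of 1.34% at 274 per arm. The coverage figures rest on two assumptions, a percentile bootstrap and side-effect rates that the article does not give. Under them the shortfall is serious up to a true rate of about 0.5%, about 2 to 5 percentage points at 1% to 3%, and negligible from about 5%. Between arms it matters mainly when one arm is at or near zero; equal low rates do not under-cover. This is a minor correction to an exploratory safety summary. It does not touch the primary analysis or the interim stopping rules.

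**What to change.** Limit the bootstrap sentence to summaries (2) and (3), and say that whole patients are resampled. For summary (1), specify Clopper-Pearson or Wilson intervals within each arm, and a Newcombe or Miettinen-Nurminen interval for the between-arm difference in proportions. If severity was the only intended scope of the bootstrap, the same wording makes that explicit.

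The cost is a sentence or so of analysis text and standard software, with no new data and no change in sample size. The only downside is somewhat wider intervals for rare side effects.
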